## Abstract

**Background:**

Feminizing gender-affirming hormone therapy (GAHT) for transgender individuals traditionally includes estradiol and androgen deprivation. Research has demonstrated that breast size as a result of GAHT in transgender women is often limited. Therefore, transgender women often choose to undergo breast augmentation surgery. Progesterone is important for breast development in cisgender women during puberty. A potential role for progesterone in breast development in transgender women has not been investigated in a randomized controlled experimental set-up. The primary objective of this study is to explore the effects on breast volume of addition of oral progesterone to GAHT with estradiol in transgender women after vaginoplasty or orchiectomy. Secondary objectives include assessment of safety, satisfaction, mood, sleep and sexual pleasure.

**Methods:**

This is a non-blinded, non-placebo, randomized controlled trial using a factorial design in adult transgender individuals assigned male sex at birth who have undergone GAHT for at least one year and underwent vaginoplasty or orchiectomy. The study design allows for rapid assessment of potential synergistic effects of various dose combinations of estradiol and progesterone on breast volume change: Ninety participants will be randomized into six groups of 15 subjects each, receiving either the baseline dose of estradiol, the baseline dose of estradiol and progesterone 200 mg daily, the baseline dose of estradiol and progesterone 400 mg daily, twice the baseline dose of estradiol, twice the baseline dose of estradiol and progesterone 200 mg daily or twice the baseline dose of estradiol and progesterone 400 mg daily, all for a duration of 12 months. The main study parameters include changes in breast volume as determined by 3D measurements. Participants will be followed-up with laboratory testing including serum progesterone concentrations as well as surveys for satisfaction, mood, sleep quality and sexual pleasure.

**Discussion:**

This study will indicate whether progesterone is safe and of additional value with regard to breast volume change in transgender individuals receiving feminizing GAHT. The results of this study will be useful for innovation of feminizing GAHT.

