### Processes, interventions and comparisons

The investigational treatment is micronized progesterone (Utrogestan®), in capsules of 100 mg. Progesterone is combined with and analyzed versus pre-defined doses of estradiol: In a 2 × 3 factorial design, the participants are randomized into six groups of 15 participants each, i.e. 90 in total (groups A-F). The intervention takes 12 months. Group A continues to receive the dose of estradiol at baseline and serves as the control group, group B receives the baseline dose of estradiol and micronized progesterone 200 mg every night at bedtime, group C receives the baseline dose of estradiol and micronized progesterone 400 mg every night at bedtime, group D receives twice the baseline dose of estradiol, group E receives the baseline dose of estradiol and micronized progesterone 200 mg every night at bedtime, group F receives twice the baseline dose of estradiol and micronized progesterone 400 mg every night at bedtime (Fig. 1A). In order to maximize adherence, progesterone is prescribed for limited 1–3 month intervals and progesterone concentrations are measured at the 6 and 12 month time points. At the time of submission of the manuscript participant recruiting was ongoing and 86 individuals had been included in the study.

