### Statistical analysis

All analyses will be performed using the most recent version of STATA. Baseline data will presented as mean with SD for normally distributed data, and median with interquartile ranges for nonnormally distributed data. Data on tobacco use and alcohol use will be presented as percentage of users. The analyses will be blinded with regard to the treatment regimen for the researcher performing the data analyses. Estradiol use will be coded as 0 (normal dosage) or 1 (double dosage), and progesterone will be coded as 0 (no use), 1 (200 mg), or 2 (400 mg). Thereafter, linear mixed model analyses with measurements clustered within participants will be performed, with breast volume as continuous outcome variable and time with set time points at 0, 3, 6, and 12 months as determinants [23]. Estradiol and progesterone use will be analyzed separately and as interaction terms. By performing analyses this way, the separate effects of estradiol and progesterone can be assessed, as well as the effects of the various treatment combinations. Breast size and volume measurements will be recorded in cc. All data are presented as mean change in cc with 95% confidence intervals. Individual-level outliers will be identified with a standardized residual cut-off point of ± 5 [24]. Non-normally distributed data will be log-transformed before mixed-model analyses. The mixed model analysis method can be used and adapted to compensate for missing values and assess potential effect modifying factors. Analyses will be stratified to treatment regimen, age, weight change and serum hormone levels. Age will be analyzed in quartiles and weight change will be assessed in 10 kg groups. Analyses for serum hormone levels will be stratified in quartiles. Satisfaction, mood, sleep, and sexual desire will be recorded as categorical variables. Sexual pleasure will be assessed using a continuous scale of the ASPI score. To analyze the relationship between satisfaction of different aspects of the breasts and breast volume, mixed model analyses will be performed. Treatment regimens, hormone levels and breast volume changes will be assessed as covariates. Side effects and adverse events will be recorded as percentages and analyzed using Fisher’s exact testing.

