We considered an average increase of 30% of breast volume – corresponding to one bra cup size increase – as a clinically relevant outcome after one year of study treatment. From previous studies, it is known that the ratio of two consecutive breast volume measurements is 1.08 with a standard deviation of 0.27 [5]. Using a power simulation model (STATA, factorialsim), in which the increase of the estradiol dose is treatment A and addition of progesterone is treatment B in a factorial design of six groups of 15 subjects, at a set alpha of 0.05 the simulated power of A is estimated at 0.95 and the power of B at 0.94.

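### The abstract promises a verdict on whether progesterone is safe, which a Fisher's exact test on 60 exposed and 30 unexposed participants cannot support

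*Protocol article*

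**What the plan says.** The abstract's Background lists safety among the secondary aims: "Secondary objectives include assessment of safety, satisfaction, mood, sleep and sexual pleasure". Its Discussion paragraph then states what the trial will deliver: "This study will indicate whether progesterone is safe and of additional value with regard to breast volume change".

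The Statistical analysis section gives one sentence on clinical events: "Side effects and adverse events will be recorded as percentages and analyzed using Fisher’s exact testing". It does not say which groups are compared, and it gives no safety margin, expected event rate or precision target. The only power statement concerns breast volume: "at a set alpha of 0.05 the simulated power of A is estimated at 0.95 and the power of B at 0.94".

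On size and duration, the section on processes, interventions and comparisons says that "the participants are randomized into six groups of 15 participants each, i.e. 90 in total (groups A-F") and that "The intervention takes 12 months". Groups B, C, E and F receive progesterone; A and D do not.

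The section on main study parameters adds liver enzymes, lipids and prolactin at 0, 6 and 12 months, and blood pressure at baseline and follow-up. Mood, stress and sleep questionnaires are also planned. The article's main Discussion is more modest than the abstract: it expects the trial to contribute knowledge of effects and side effects.

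**The concern.** A significance test can show that events are more frequent on progesterone. A non-significant result cannot show that they are not, unless the study was large enough to make a relevant excess unlikely to be missed. The sample was sized on breast volume, and nothing in the text shows that it suffices for events. Abstracts are widely read on their own, and this one promises an answer on safety. If the event analysis consists of percentages and p-values, it contains nothing that tells a reader how large an excess is still compatible with the data.

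**Working it through.** **Inputs from the article.** 15 per group, so 4 × 15 = 60 on progesterone and 2 × 15 = 30 on none; alpha 0.05; background breast-volume ratio 1.08 with SD 0.27; target increase 30%. **Assumed:** two-sided testing, no dropout, and all event rates, since the article gives none. Control rates of 0–30% and excesses of 5–30 percentage points were tried.

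**1. The plan's own power figure (breast volume).** Take the difference as 1.30 − 1.08 = 0.22; this is a reading of the text.
- Estradiol, 45 v 45: SE = 0.27 × √(1/45 + 1/45) = 0.0569; 0.22/0.0569 − 1.96 = 1.905; power 0.97 (stated 0.95).
- Any progesterone v none, 60 v 30: SE = 0.27 × √(1/60 + 1/30) = 0.0604; 0.22/0.0604 − 1.96 = 1.684; power 0.95 (stated 0.94).

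The stated figures are thus roughly reproduced by comparing factorial margins. The most favourable event comparison for progesterone is the same margin, 60 v 30.

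**2. Power of Fisher's exact test, 60 v 30.** Power = Σₐ Σ_b Bin(a; 60, p₁) × Bin(b; 30, p₀) × 1{Fisher p(a, b) ≤ 0.05}, summed over all outcomes, where p₀ is the rate without progesterone and p₁ is p₀ plus the excess.

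| Control rate | +5 points | +10 | +15 | +20 | +25 | +30 |
|---|---|---|---|---|---|---|
| 0% | 0.010 | 0.248 | 0.695 | 0.933 | 0.991 | 0.999 |
| 2% | 0.032 | 0.245 | 0.526 | 0.755 | 0.905 | 0.973 |
| 5% | 0.057 | 0.193 | 0.403 | 0.648 | 0.836 | 0.938 |
| 10% | 0.054 | 0.159 | 0.346 | 0.562 | 0.744 | 0.869 |
| 20% | 0.063 | 0.141 | 0.265 | 0.430 | 0.616 | 0.783 |
| 30% | 0.055 | 0.121 | 0.242 | 0.412 | 0.599 | 0.765 |

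For a 10-point excess, one dose v none (30 v 30) has power of 7–10%, and one group v another (15 v 15) has 1–4%.

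**3. Zero events.** The one-sided 95% upper limit is 1 − 0.05^(1/n): 4.9% for n = 60, 9.5% for n = 30 and 18.1% for n = 15. If the true rate is 1%, the chance of seeing any event in 60 is 1 − 0.99^60 = 45%.

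**4. What an interval would show.** Suppose 10% have an event in both groups, 6/60 v 3/30. The Wilson 95% limits are 4.66% to 20.15% and 3.46% to 25.62%. Newcombe's limits for the difference are −√[(10 − 4.66)² + (25.62 − 10)²] = −16.5 points and +√[(20.15 − 10)² + (10 − 3.46)²] = +12.1 points. A Fisher p-value from the same data would not show that an excess of 12 points remains possible.

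**The case against.** The other side has several fair arguments.

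- **No such rule is written.** A reader might infer that the plan will treat a non-significant test as proof of safety. The article does not say so, and that charge is not supported. What stands is narrower: the abstract promises an indication on safety, and the named event analysis cannot supply one from a null result.
- **Safety does not rest on Fisher's test alone.** This is correct. Laboratory values, blood pressure and mood scales are also collected, and they bear on concerns that the Background raises, such as HDL cholesterol and mood swings. They do not show whether clinical events are more frequent, and for those Fisher's test is the only method named.
- **Power depends on the assumed rates.** This is also correct. It would be tempting to say that power is below 20% throughout. That holds for excesses up to 10 points over control rates of 5% or more, but not for rarer background events or larger excesses.
- **The trial is exploratory and a possible pilot, and its main Discussion is cautious.** True, and this makes the abstract sentence the outlier.
- **Low power for events is normal, Fisher's test is valid for sparse counts, and interval reporting may be left to a fuller plan.** Low power and the lack of interval details are not faults by themselves in a condensed article. The difficulty is that the stated claim, the stated test and the stated sample size do not fit together, and a fuller plan cannot change 60 v 30.

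**Conclusion.** The point holds as a mismatch between one sentence of the abstract and the design. Under the assumed rates, the best available event comparison would miss a 10-point excess at least three times in four, and a 15-point excess over control rates of 5–10% about 60–65% of the time. Power of 80% needs about 25–30 points over control rates of 5–10%; with almost no background events, about 20 points is enough. Zero events among all 60 exposed would exclude only rates above about 5% (one-sided 95%). The trial can describe common side effects over 12 months, but it cannot settle whether progesterone is safe.

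These figures assume a two-sided test and complete follow-up; losses would generally lower the power. The count of 60 exposed does not depend on the estradiol dose in group E. No figure stated in the plan is shown to be wrong here, and the breast-volume analysis is not affected.

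**What to change.** 1. **Analysis of adverse events.** Make the risk difference with its 95% confidence interval the basis for inference, in place of Fisher p-values. Do this for any progesterone v none (60 v 30) and for double v baseline estradiol. The latter is 45 v 45 under the Fig. 1 legend. The text of the section on processes, interventions and comparisons gives group E a different estradiol dose from that legend, and the two must be reconciled first.
2. **Zero counts and listings.** Give exact upper limits where no events occur, and list events by group descriptively.
3. **Abstract.** Bring the Discussion paragraph into line with the main Discussion: the study describes side effects and estimates their frequency. State that zero events in 60 exposed participants excludes only rates above about 5% (one-sided 95%).

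The cost is a few lines of analysis and some rewording, with no extra participants or measurements. The downside is a more modest safety claim.

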**Trial registration:**

WHO International Clinical Trials Registry Platform: EUCTR2020-001952-16-NL; date of registration: 12 December 2020 https://trialsearch.who.int/Trial2.aspx?TrialID=EUCTR2020-001952-16-NL.

## Background

Transgender people experience an incongruence between their sex assigned at birth and their gender identity. In the Netherlands, it is estimated that 1:2,800 birth-assigned males and 1:5,200 birth-assigned females undergo or have undergone gender-affirming treatment [1]. Transgender individuals with the male sex assigned at birth who receive feminizing gender-affirming hormone therapy (GAHT) traditionally use estradiol and anti-androgenic treatment before they can choose to undergo vaginoplasty or orchiectomy [2, 3]. In this report, we will use the term transgender women for individuals who were assigned the male sex at birth and use feminizing hormone therapy. After gender-affirming surgery, hormone therapy replaces endogenous hormone production. Research has demonstrated that breast size as a result of GAHT in transgender women is often limited and that therefore transgender women often choose to undergo breast augmentation surgery [4, 5].

Progesterone is the natural ligand of the progesterone receptor (PR). In both cisgender (alignment of sex as-signed at birth and gender identity) men and women progesterone is synthesized in the adrenal glands and in pre-menopausal cisgender women the primary source is in the ovaries. The estrogen receptors and progesterone receptor (PR) are expressed in many tissues in the human body and regulate gene expression and cell differentiation. In addition to estradiol, progesterone has an important role in mammary and breast development during female puberty: Estradiol stimulates the expansion of breast tissue and progesterone stimulates differentiation of the mammary tissue [6, 7]. A potential role for progesterone has not been investigated with regard to breast development in transgender women in a randomized controlled fashion. In addition to estradiol, transgender women are frequently treated with anti-androgens. In our center, in the past, cyproterone acetate, an anti-androgen with progestogenic characteristics - now replaced with GnRH agonists - was most often used to lower testosterone levels before vaginoplasty or orchiectomy, which is a reason progesterone has not been included in the treatment. In other countries, in particular in the United States where cyproterone acetate is not available, progesterone is more often added to GAHT. However, whether this has a beneficial effect on breast development is not clear as evidence is lacking [8]. Since the addition of progesterone is theoretically beneficial, this is a persisting subject of international debate.

Only few studies have addressed the effect of addition of the progestin medroxyprogesterone acetate (MPA) to estradiol (and anti-androgen) treatment in transgender women: In a small group of transgender women, no differences in breast size were observed relative to transgender women receiving estrogens only [9]. In a retrospective uncontrolled study, transgender women reported increased breast volume when using MPA. Side effects were rare and most frequently included mood swings [10]. In 2019, Prior suggested oral natural progesterone to have several additional feminizing effects when incorporated into the hormonal treatment of transgender women, including increased breast and areolar size. Furthermore, progesterone might have beneficial effects regarding cardiovascular and breast cancer risk, mood, and sleep quality [11]. In cisgender women, the progesterone surge during the luteal phase is associated with a decrease of sexual desire [12]. In a recent retrospective study, progesterone was not shown to make any discernable difference in satisfaction with libido compared with standard GAHT regimens [13]. Also, a case-control study was published in which participants received a low dose of 100 mg micronized progesterone in addition to estradiol GAHT for a period of three months. In this study, no significant breast volume changes were observed [14].With regard to side effects, progestin use has been linked to decreased high-density lipoprotein (HDL) cholesterol levels in transgender women [15]. In general, transgender women have a lower risk of developing breast cancer, compared with cisgender women [16]. The hormone progesterone is widely used as hormone replacement therapy in cisgender women and during in vitro fertilization procedures and has not been demonstrated to increase breast cancer risk [17]. The use of micronized progesterone has not been associated with increased risk of venous thromboembolism in cisgender women [18].

This study aims to explore the effects of addition of progesterone to estradiol treatment and increasing estradiol doses on breast volume with regard to breast size in transgender women. Secondary objectives include assessment of the effects of progesterone combined with estradiol on satisfaction with breast volume, mood and sleep quality, sexual pleasure, side effects of the treatment regimen, as well as serum progesterone concentrations.

## Methods/design

### Aim, design and setting of the study

In order to determine the effects and side effects of adding oral progesterone to feminizing GAHT, we set up a non-blinded, non-placebo, randomized controlled trial, using a 2 × 3 factorial design. This study design allows for rapid assessment of potential effects of progesterone treatment and dose combinations on breast volume and may serve as a pilot project for a larger study in transgender women at the start of hormone treatment before surgery. This is a mono-center study at the Center of Expertise on Gender Dysphoria of Amsterdam UMC, location VUmc, a national referral center for individuals experiencing gender incongruence.

### Characteristics of participants

Individuals who regularly visit the clinic are eligible to participate, provided that the individual started GAHT after 18 years of age (to eliminate potential effects of puberty suppression), received more than one year of GAHT, underwent vaginoplasty or orchiectomy (to avoid interference from androgen deprivation strategies), has sufficient knowledge of the Dutch language and a BMI 18–30 kg/m2. A potential subject who meets any of the following criteria will be excluded from participation in this study: previous use of progesterone/ progestin (not including cyproterone acetate or oral contraceptives), history of breast augmentation or reduction surgery, active treatment for depression, current use of progesterone/ progestin including cyproterone acetate, severe familial dyslipidemia (e.g. Familial Hypercholesterolemia), serum estradiol concentration > local reference range (200–400 pmol/L) at last visit prior to baseline, contraindications for the use of micronized progesterone, history of epilepsy (because of the oscillating 3D scanner).

### Processes, interventions and comparisons

The investigational treatment is micronized progesterone (Utrogestan®), in capsules of 100 mg. Progesterone is combined with and analyzed versus pre-defined doses of estradiol: In a 2 × 3 factorial design, the participants are randomized into six groups of 15 participants each, i.e. 90 in total (groups A-F). The intervention takes 12 months. Group A continues to receive the dose of estradiol at baseline and serves as the control group, group B receives the baseline dose of estradiol and micronized progesterone 200 mg every night at bedtime, group C receives the baseline dose of estradiol and micronized progesterone 400 mg every night at bedtime, group D receives twice the baseline dose of estradiol, group E receives the baseline dose of estradiol and micronized progesterone 200 mg every night at bedtime, group F receives twice the baseline dose of estradiol and micronized progesterone 400 mg every night at bedtime (Fig. 1A). In order to maximize adherence, progesterone is prescribed for limited 1–3 month intervals and progesterone concentrations are measured at the 6 and 12 month time points. At the time of submission of the manuscript participant recruiting was ongoing and 86 individuals had been included in the study.

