**Fig. 1 Fig1:**
[figure not shown]
Study set-up. (**A**) Ninety participants will be randomized into six groups of 15 subjects each, receiving either the baseline dose of estradiol (group A), the baseline dose of estradiol and progesterone 200 mg daily (**B**), the baseline dose of estradiol and progesterone 400 mg daily (**C**), twice the baseline dose of estradiol (**D**), twice the baseline dose of estradiol and progesterone 200 mg daily (**E**), or twice the baseline dose of estradiol and progesterone 400 mg daily (**F**). (**B**) The study will include 12 months of follow-up after the start of the intervention. Visits are scheduled at baseline, after 3, 6 and 12 months

The established feminizing hormone therapy for transgender women after vaginoplasty or orchiectomy consists of estradiol, prescribed as tablets, patches, gel or spray. The baseline dose of estradiol (groups A, B, C) is defined as oral estradiol valerate (Progynova®), or estradiol hemihydrate tablets (generic, Estradiol Sandoz®, Estrofem®, Zumenon®), or transdermal estradiol patches (Systen®, Sandoz®), estradiol gel (Oestrogel®) or spray (Lenzetto®) resulting in serum estradiol concentrations of 200–400 pmol/L, which are the current local reference ranges. Twice the baseline dose of estradiol (groups D, E, F) is defined as doubling of the estradiol dose of the participant at study entry in order to achieve and maintain serum estradiol concentrations of 400–800 pmol/L. These higher concentrations can be considered safe as these are within the reference ranges stated in the international guideline for hormone treatment of gender dysphoria [2].

Two doses of micronized progesterone are tested in order to investigate a potential dose-response effect. If a dose-response relation is established, this would support a biological effect of the treatment. The duration of the study will be approximately three years in total and will include 12 months of patient follow-up after the start of the intervention (Fig. 1B). Visits are scheduled at baseline, after 3, 6 and 12 months. The study protocol is in line with the Standard Protocol Items: Recommendation for Interventional Trials (SPIRIT) guidelines (Fig. 2).

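### Group E is given the same regimen as group B in the interventions text but doubled estradiol in Fig. 1 and the dose definitions; read literally, the 2 × 3 factorial has an empty cell

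*Protocol article*

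**What the plan says.** The interventions section announces a full factorial: "In a 2 × 3 factorial design, the participants are randomized into six groups of 15 participants each, i.e. 90 in total (groups A-F"). It then lists the arms one by one. For the second arm, "group B receives the baseline dose of estradiol and micronized progesterone 200 mg every night at bedtime". For the fifth, "group E receives the baseline dose of estradiol and micronized progesterone 200 mg every night at bedtime". The neighbouring arms in the doubled half are described as expected: "group D receives twice the baseline dose of estradiol" and "group F receives twice the baseline dose of estradiol and micronized progesterone 400 mg every night at bedtime". The list ends by pointing to Fig. 1A.

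Elsewhere group E is different. The Fig. 1 legend gives it, by letter, doubled estradiol with 200 mg progesterone. The text below the figure limits the baseline stratum to groups A, B and C and continues: "Twice the baseline dose of estradiol (groups D, E, F) is defined as doubling of the estradiol dose of the participant at study entry". The Methods paragraph of the Abstract uses no group letters, but its six regimens include "twice the baseline dose of estradiol and progesterone 200 mg daily", which appears nowhere in the interventions list.

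The Statistical analysis section codes estradiol 0/1 and progesterone 0/1/2 and plans to analyse the two separately and as interaction terms. The Discussion presents the study of synergy as a purpose of the factorial design.

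**The concern.** The conflict concerns the treatment definition of one of six arms, in a trial whose question is about dose combinations. A reader, replicator or meta-analyst working from the interventions text would record five regimens, 60 participants on baseline estradiol and 30 on doubled estradiol. One working from Fig. 1 would record six regimens and a 45/45 split.

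Two things would be at stake if the interventions text had been followed. First, the cell for doubled estradiol with 200 mg would hold nobody, so one of the two planned interaction contrasts would have no data. Second, if group E were treated as that text says but carried estradiol code 1, as the dose definitions imply, a third of the nominally doubled participants would not have been doubled and the estradiol effect would be biased towards zero. Recruitment was nearly complete at submission (86 of 90), so allocations already existed. The published text alone does not show which description they followed.

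**Working it through.** **Passages side by side**

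| Place | Estradiol in E | Progesterone in E |
|---|---|---|
| Interventions list | baseline | 200 mg |
| Fig. 1 legend | twice baseline | 200 mg |
| Definitions below Fig. 1 | twice baseline (D, E, F) | not stated |
| Abstract, fifth regimen (no letter) | twice baseline | 200 mg |

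**Inputs.** Six groups of 15; ratio of consecutive volumes 1.08 with SD 0.27; relevant increase 30%; alpha 0.05; stated power 0.95 (estradiol) and 0.94 (progesterone), all from the article. Assumed, because the article does not say: a two-sided test, and a difference of 1.30 − 1.08 = 0.22 entered in the simulation.

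**Step 1: the plan's own figures.** N = 6 × 15 = 90. Noncentral t with 84 df and SD 0.27:
- estradiol, 45 v 45: power 0.969 (stated 0.95);
- progesterone, any v none, 60 v 30: power 0.950 (stated 0.94).

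Both lie within two points of the stated values. A difference of 0.30 gives more than 0.998 for both and does not reproduce them. The stated power is thus consistent with six distinct cells.

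**Step 2: cells under each description (n)**

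| | No progesterone | 200 mg | 400 mg |
|---|---|---|---|
| Baseline E2, per Fig. 1 | 15 | 15 | 15 |
| Doubled E2, per Fig. 1 | 15 | 15 | 15 |
| Baseline E2, per interventions list | 15 | 30 | 15 |
| Doubled E2, per interventions list | 15 | 0 | 15 |

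The interaction model has six columns: intercept, estradiol, two progesterone indicators and two products. Its rank is 6 under Fig. 1 and 5 under the interventions list, so the estradiol × 200 mg term is not estimable.

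**Step 3: precision of the estradiol effect.** In the additive model with two progesterone indicators, each progesterone level contributes information n₀n₁/(n₀+n₁), where n₀ and n₁ are the numbers on baseline and doubled estradiol.
- Fig. 1: 3 × (15 × 15/30) = 22.5; SE = 0.27/√22.5 = 0.057.
- Interventions list: 7.5 + 0 + 7.5 = 15; SE = 0.27/√15 = 0.070.

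Power at 0.22 is 0.97 under Fig. 1 and 0.88 under the interventions list, by noncentral t and by normal approximation alike.

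**Step 4: treated as listed, coded as doubled.** The 200 mg level then contributes a true difference of zero. The estimated effect is 0.22 × 30/45 = 0.147. With SE 0.057, 0.147/0.057 ≈ 2.58, and power is about 0.72 (noncentral t) or 0.73 (normal).

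**Sensitivity**
- If progesterone enters as a linear score 0/1/2, power for estradiol under the interventions list is 0.95 rather than 0.88 (normal approximation; 0.97 with six full cells). The interaction at 200 mg would then rest on linearity in dose, with no observations in that cell.
- At a difference of 0.30, power under the interventions list is 0.99 with the two indicators.

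**The case against.** The strongest reply is that this is one faulty clause and not an unsettled design. The Abstract, the Fig. 1 legend, the dose definitions and the factorial label in the same paragraph all describe six distinct cells, and so does the stated power. The 86 participants were presumably enrolled under a full protocol that is not shown, and a clause in an article is no evidence that anyone was treated according to it. The power losses need events that no passage reports, an effect size the article does not state, and a single-ratio additive model in place of the planned mixed model over four time points.

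Much of this stands. A drafting slip is plausible, no treatment error is shown, and the power figures are illustrative and conditional. It does not remove the finding: the current text gives two incompatible treatments for the same arm, and nothing in the article says which statement prevails. The contradiction and the empty cell follow from the wording alone and do not depend on the 0.22.

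**Conclusion.** The concern holds. The article contradicts itself on the estradiol dose of group E, 15 of 90 participants, in text that defines the interventions. It must be corrected.

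Taken literally, the interventions list turns six regimens into five and leaves the doubled-estradiol plus 200 mg cell empty. The conditional costs for the estradiol effect are a rise in SE from 0.057 to 0.070 with power down from 0.97 to 0.88, or an effect diluted to 0.147 with power about 0.72 if treatment and coding disagree. They rest on a two-sided 0.05 test, SD 0.27, an assumed difference of 0.22 and categorical progesterone. This point takes no position on which regimen is clinically right.

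**What to change.** Reconcile the interventions list with the Abstract, the Fig. 1 legend and the dose definitions, using the approved protocol, the randomisation list and the prescription records. Confirm what group E participants were assigned and prescribed, and correct whichever text is wrong so that every place describes the same arm.

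Only if some group E participants were treated under the other description: state how they are coded in the estradiol factor, say which interaction contrasts remain estimable, and restate the power.

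The cost is a one-sentence correction and a records check for one arm of 15.
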